### Statistical and analytical plan

Patients will be analyzed according to the intention-to-treat principle. Analyses will be conducted at the Shaanxi Cerebrovascular Disease Clinical Research Center by blinded biostatisticians. Baseline characteristics will be summarized using univariate analyses. Categorical variables will be presented as the number and percent, whereas the continuous variables will be presented as mean (± standard deviation) or median (interquartile range). We will compare the proportions for the primary and secondary outcomes between patients randomized to the individualized BP-lowering group vs the guideline-recommended BP-lowering group using the Chi-square test. We will calculate the relative risk reduction, absolute risk reduction, and the number needed to treat with individualized BP-lowering target to prevent one death. Logistic multivariate analyses will be used to adjust for potential confounding effects of different variables and estimate adjusted odds ratios and associated 95% confidential intervals. Two-sided *p* values ≤ 0.05 will be considered significant. Statistical analysis will be performed with SPSS version 22 software (SPSS Inc., Chicago, IL, USA).

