**Methods/design:**

The CHASE trial is a multicenter, randomized, controlled study. A total of 500 adult patients with acute severe stroke will be enrolled in 18 study sites in China and randomized to individualized BP lowering (10–15% reduction from admission level) or guideline-recommended BP lowering. The primary outcome measurement is the proportion of participants with a poor outcome (modified Rankin Scale ≥ 3) at day 90 of enrollment. Secondary outcomes include disability at hospital discharge and the ability of activities of daily living at day 90 of enrollment. The relationship between intervention and the primary outcome will be analyzed using multivariate logistic regression adjusted for study site, demographics, and baseline characteristics.

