### Outcome measurement

The primary outcome measurement is the proportion of participants with a poor outcome at day 90 of enrollment. Poor outcome is defined as major disability (mRS ≥ 3, unable to live independently) or all-cause death. The proportion of participants with a poor outcome at hospital discharge is the key secondary outcome. Other secondary outcomes are the disability (evaluated by NIHSS, GCS, and Barthel index) at hospital discharge and the ability of activities of daily living at day 90 of enrollment evaluated by Barthel index. Outcomes are assessed independently by trained research assistants who are blind to the grouping results and clinical data. The 90-day outcomes are evaluated via telephone interviews at day 90 of enrollment (a delay of up to three days is acceptable). In cases when the patient is incapable to complete the interview, the first choice for a proxy is the spouse/live-in companion.

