### Determination of the sample size

The sample size was set at 500 to provide at least 80% power to detect a 6% absolute risk reduction in the primary outcome for patients in the individualized BP-lowering group compared to those in the guideline-recommended control group, using a two-sided significance test with 5% type I error. The following assumptions were made: a primary outcome of 60% in the control group will be reduced to 54% in the individualized group; and there will be 10% non-adherence to the treatment protocol and 5% overall loss to follow-up. The 60% incidence of unfavorable 90-day outcome is extrapolated from one Chinese study on severe stroke (NIHSS > 10) in 2013 [17]. The 10% non-adherence rate and the absolute risk reduction in primary outcome are extrapolated from the INTERACT1&2 studies which were designed to compare the effects of two different BP-lowering strategies in acute stroke patients [8, 18].

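### The abstract and the analysis section give different analyses of the primary outcome, an adjusted logistic model and an unadjusted chi-square test, and neither is named as decisive

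*Protocol article*

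**What the plan says.** The primary outcome is binary. Under Outcome measurement: "The primary outcome measurement is the proportion of participants with a poor outcome at day 90 of enrollment", where poor outcome means mRS of 3 or more, or death from any cause.

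Two places say how it will be analysed.

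- **Abstract, Methods/design:** "The relationship between intervention and the primary outcome will be analyzed using multivariate logistic regression adjusted for study site, demographics, and baseline characteristics". No other test is mentioned.
- **Statistical and analytical plan:** "We will compare the proportions for the primary and secondary outcomes between patients randomized to the individualized BP-lowering group". The comparator is the control arm, and the method named is a chi-square test. Relative and absolute risk reductions follow. Then: "Logistic multivariate analyses will be used to adjust for potential confounding effects of different variables", giving adjusted odds ratios with confidence intervals.

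The only decision rule in the analysis section is that two-sided p "values ≤ 0.05 will be considered significant". The sample size section speaks of "using a two-sided significance test with 5% type I error" and does not say which test.

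**The concern.** The trial makes one superiority claim, and the article gives two tests that could decide it. A reader of the Abstract expects the adjusted odds ratio to settle the matter. A reader of the analysis section can reasonably expect the chi-square test to do so. The covariates differ as well: the Abstract names classes, and the analysis section refers only to unspecified variables.

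The two analyses also estimate different things. The chi-square test goes with a marginal difference in proportions, while the logistic model gives an odds ratio conditional on covariates.

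Three things are at stake. The 5% error rate is not guaranteed if either result can be claimed. The article has no rule for the case where the two tests disagree. And if the chi-square test turns out to be decisive, prognostic information already recorded at screening does not contribute to the primary test.

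**Working it through.** **1. The two texts side by side**

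| | Abstract | Statistical and analytical plan |
|---|---|---|
| Test of the primary outcome | Adjusted logistic regression | Chi-square, then logistic models |
| Covariates | Study site, demographics, baseline characteristics | Not named |
| Called primary or supportive | No | No |
| Tied to p ≤ 0.05 | No | Neither analysis specifically |

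**2. The plan's own figure.** Inputs from Determination of the sample size: 60% vs 54%, two-sided 5%, at least 80% power, N = 500, 5% loss. The pooled-variance formula for two proportions is

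n per arm = [1.960·√(2·0.57·0.43) + 0.8416·√(0.60·0.40 + 0.54·0.46)]² / 0.06² = [1.3723 + 0.5882]² / 0.0036 ≈ 1,068,

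which is 2,136 in total. The stated 500 does not reproduce. With 500 × 0.95 = 475 evaluable (237.5 per arm), power is

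Φ[(0.06·√237.5 − 1.3723) / 0.6989] = Φ(−0.640) = 26.1%.

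That shortfall is a separate matter. Here it serves as a check on the simulated chi-square power below.

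**3. Simulation of the two tests.** There were 475 evaluable patients, 1:1 allocation, a 60% control rate and 4,000 trials per setting. Each trial was tested by the uncorrected chi-square test and by the Wald test of treatment in a logistic model adjusted for one standard-normal prognostic score. The slope of that score is an assumption; the article gives no prognostic strength. Neither site effects nor the 10% non-adherence were modelled.

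Disagreement means that exactly one test is significant: 2 × either − chi-square − adjusted. At slope 0.5, for example, 2 × 29.7 − 26.4 − 27.2 = 5.8.

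| Slope per SD (AUC) | No effect: chi-square / adjusted / either | 60% vs 54%: chi-square / adjusted / either | Tests disagree at 60% vs 54% | Adjusted minus chi-square power |
|---|---|---|---|---|
| 0.5 (0.63) | 5.1 / 5.3 / 6.3% | 26.4 / 27.2 / 29.7% | 5.8% | 0.8 points |
| 1.0 (0.74) | 5.1 / 5.3 / 7.0% | 26.9 / 29.6 / 34.4% | 12.3% | 2.7 points |
| 1.5 (0.81) | 5.0 / 5.5 / 7.8% | 26.4 / 33.2 / 38.3% | 17.0% | 6.8 points |
| 2.0 (0.86) | 4.8 / 4.5 / 7.0% | 25.9 / 37.7 / 42.4% | 21.2% | 11.8 points |

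Monte Carlo error is about 0.4 points for type I error and 0.7 for power. The chi-square power of 25.9–26.9% agrees with the 26.1% from the formula.

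A further run of the same design at slope 1.8 (AUC 0.84) gave 36.3 − 25.6 = 10.7 points of power difference. Another set over slopes 0.5–1.8 gave 5.8–8.2% for at least one significant test under no effect, disagreement in 6–21% of trials, and adjusted power of 27–37% against 27% by chi-square.

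**4. Different quantities.** At the planned rates the risk difference is 6 points and the marginal odds ratio is (0.54/0.46)/(0.60/0.40) = 0.78. With prognostic covariates in the model, the conditional odds ratio is not the same number.

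**The case against.** The strongest reply is that the two sections are compatible. The analysis section contains both analyses, the Abstract mentions one of them, and reporting an unadjusted comparison beside an adjusted odds ratio is ordinary practice. There is even a hint of order: the trial is sized on a difference in proportions, the chi-square test comes first, and the logistic model follows as estimation. This stands in part. The difficulty is that the one analysis the Abstract keeps is the one this reading makes secondary, so the order cannot be inferred safely.

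It is also fair that an exact covariate list is commonly left to an analysis plan that is not shown. The missing list is therefore not the finding; the unresolved choice of test is. Naming the chi-square test as primary would control the error rate equally well.

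Some stronger readings are tempting and not supported:

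- **That the trial intends to pick the better p value.** The article states no such intention. The 6–8% is what the wording permits.
- **That precision is lost in any case.** It is lost only if the chi-square test decides, and hardly at all with a weak covariate.
- **That covariates will be searched for.** With four assumed covariates and free choice of any subset, a simulation gave a false-positive rate of about 10%, against 5.1% with all four fixed. But the article describes no selection procedure. Its mention of confounding is loose wording for a randomized trial and shows nothing more.

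**Conclusion.** The concern holds as an unresolved choice of primary test. Two analyses are given for one superiority claim, and neither the decision rule nor the sample size section settles which one counts.

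The size is modest. For assumed slopes of 0.5–1.8 per SD and one fixed prognostic score:

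- type I error is about 6–8% instead of 5% if either result may be claimed;
- the tests disagree in about 6–21% of trials at 60% vs 54%;
- about 0 to 11 points of power are forgone if the chi-square test decides.

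The inflation stays small because the two tests are highly correlated. With either analysis named alone, the error rate remains near 5%.

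A reader might infer that adjustment would rescue the trial's power. It would not: adjusted power at the planned effect stayed below 40% in every setting tried.

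**What to change.** Make the Abstract and the Statistical and analytical plan say the same thing, before unblinding:

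1. The single primary test is the treatment term in one logistic regression of poor outcome at day 90, two-sided at 5%. Tie the significance rule to that test.
2. Fix the covariates in advance, from the classes the Abstract names and from data already available. Site, age, sex, stroke type and baseline NIHSS are one example. The exact list and the handling of site are for the trial team to choose; the simulations did not test a particular model.
3. Label the chi-square test and its risk difference as supportive.
4. Report an adjusted risk difference with its 95% confidence interval beside the adjusted odds ratio.

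The cost is a change of wording and no new data, since Study procedures already records demographics, stroke subtype and NIHSS at screening. The downsides are small: the covariate set can no longer be varied, and the headline effect becomes a conditional odds ratio, which is why item 4 is needed. Follow-up is reported as ongoing and the biostatisticians as blinded, so the choice can still be made credibly if unblinding has not occurred. The sample size shortfall needs its own correction.

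### The trial is sized on a risk difference, but the only adjusted measure named is an odds ratio, and the planned NNT is for death rather than for the primary outcome

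*Protocol article*

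**What the plan says.** Four statements in the protocol article bear on this.

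- **Design effect** (Determination of the sample size): the assumption is "a primary outcome of 60% in the control group will be reduced to 54% in the individualized group", and the trial claims "at least 80% power to detect a 6% absolute risk reduction in the primary outcome". The effect is a risk difference.
- **Absolute measures** (Statistical and analytical plan): directly after the Chi-square comparison of proportions comes "We will calculate the relative risk reduction, absolute risk reduction, and the number needed to treat". The sentence goes on to define the NNT as the number treated to prevent one death.
- **Adjusted measure** (same section, next sentence): logistic models will adjust for potential confounders and "estimate adjusted odds ratios and associated 95% confidential intervals".
- **Adjustment set** (Abstract, Methods/design): the intervention's relationship with the primary outcome is to be analyzed by "multivariate logistic regression adjusted for study site, demographics, and baseline characteristics".

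Under Outcome measurement, the primary outcome is major disability (mRS ≥ 3) or death from any cause at day 90.

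**The concern.** The design question is how many percentage points of poor outcome the individualized target removes. The adjusted analysis, which the Abstract presents as the analysis of the primary outcome, answers on the odds scale only. Two things follow.

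First, with about 60% of patients having the event, an odds ratio lies well away from the risk ratio. Adjustment moves it further from 1 even when baseline is perfectly balanced, because odds ratios are non-collapsible. A reader who sees a crude risk difference beside an adjusted odds ratio cannot tell how much of the apparent change comes from chance imbalance and how much from the change of measure.

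Second, the same fitted model can return an adjusted risk difference, usually with a smaller standard error than the crude one if the covariates predict outcome. As the article reads, that gain is not taken.

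A related mismatch is that the NNT is tied to death alone, while the trial is sized and primarily analyzed on disability or death.

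**Working it through.** **Inputs from the article.** 500 patients randomized 1:1, so 250 per arm; poor outcome 60% (control) and 54% (individualized); two-sided 5% test; 18 sites; "10% non-adherence to the treatment protocol and 5% overall loss to follow-up". **Assumed, because the article gives no figure:** the prognostic strength of the covariates, expressed as the SD of a normal score on the logit scale, from 0 to 2.0.

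**1. The plan's own figure.** With mean risk 0.57, the pooled two-proportion formula gives, per arm,

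[1.960·√(2·0.57·0.43) + 0.842·√(0.60·0.40 + 0.54·0.46)]² / 0.06² = (1.372 + 0.588)² / 0.0036 ≈ 1,068,

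or 2,136 in total before any allowance for loss or non-adherence. The stated 500 is not reproduced; it gives about 27% power for 6 points. That is a separate and much larger problem. It matters here only because precision is scarce.

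**2. The same effect on different scales.**
- Risk difference: 0.60 − 0.54 = 0.06; NNT for poor outcome 1/0.06 = 16.7.
- Risk ratio: 0.54/0.60 = 0.90.
- Marginal odds ratio: (0.54/0.46)/(0.60/0.40) = 0.783.
- If 0.783 were misread as a risk ratio: 0.60·(1 − 0.783) = 0.13, that is 13 points and an NNT of 7.7.

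**3. Conditional odds ratio.** For a normal score with SD s, solve for the intercepts that make the average risks 0.60 and 0.54, and exponentiate their difference. R² is the variance of the predicted risk divided by 0.60·0.40.

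| SD of score (assumed) | R² | Conditional OR |
|---|---|---|
| 0 | 0 | 0.78 |
| 1.0 | 0.17 | 0.74 |
| 1.5 | 0.29 | 0.71 |
| 2.0 | 0.39 | 0.67 |

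The marginal effect is 6 points in every row.

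**4. Precision of the risk difference.** Crude: SE = √[(0.2400 + 0.2484)/250] = 0.0442, so a 6-point difference has a 95% CI of about −2.7 to 14.7 points. For the standardized version, fit the logistic model, predict every patient's risk under each arm, and average the differences. In simulated trials of 500 it has the same mean, about 6 points. The approximate analytic saving in SE is 1 − √(1 − R²).

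| SD of score | Analytic | Simulated, score only | Simulated, plus 17 site terms and 6 non-prognostic covariates |
|---|---|---|---|
| 0 | 0% | 0% | SE rises about 2% |
| 0.5 | about 3% | about 2–3% | about 0% |
| 1.0 | 9% | about 9% | about 6% |
| 1.5 | 16% | about 15% | about 13% |
| 2.0 | 22% | about 21% | about 19% |

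The last column is the one to use, because the Abstract names study site and several baseline variables as covariates. The number of non-prognostic covariates is also an assumption. Simulation error is about one percentage point.

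**5. What this means for the interval.** The crude half-width is 1.96·0.0442 = 8.7 points. A 6% saving gives 1.96·0.0442·0.94 = 8.1 points; a 19% saving gives 1.96·0.0442·0.81 = 7.0 points. With the normal approximation Φ(0.06/SE − 1.96), power moves from about 27% to about 30% and 39%, still far below 80%.

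**6. The NNT.** Step 2's 16.7 is for the composite. The NNT that the article plans counts deaths. No death rate is assumed anywhere in the article, and a model for poor outcome does not yield a risk difference for death.

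**The case against.** The strongest reply is that nothing here is incorrect. Randomization makes the crude risk difference valid and unbiased; it is on the design scale, and it is planned. A Chi-square test with absolute measures, followed by an adjusted odds ratio, is conventional reporting. That the risk reductions stay crude is inferred from the order of two sentences in a condensed article, and an analysis plan that is not shown could specify standardization. The gain depends on covariate strength that nobody has stated, and could be nil. All of this stands, and it keeps the point minor.

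Three stronger readings are tempting, and the document supports none of them.

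- A reader might infer that the crude risk difference is biased or that the design question goes unanswered. It is neither biased nor missing; it is only less precise than it could be.
- A reader might infer that the crude and adjusted results conflict or cannot be set side by side. They are different, individually valid measures that share the null value of no effect. Non-collapsibility is not bias.
- A reader might infer that the planned NNT loses precision that the planned model would supply. It does not, since that NNT is for death and the model is for poor outcome.

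What the objection does not remove is that the article itself names the odds ratio as the adjusted measure, and that it attaches the NNT to an outcome other than the primary one. Both are written in the text.

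**Conclusion.** The point holds as a minor improvement: lost precision and mixed effect scales, plus an NNT that does not match the primary outcome. At 60% versus 54% the risk ratio of 0.90 corresponds to a marginal odds ratio of 0.78 and a conditional one of about 0.74 to 0.67. Standardization would reduce the SE of the risk difference by about 6% to 19% for a prognostic score of SD 1.0 to 2.0, with no gain at SD 0.5 and a loss of about 2% at SD 0. These figures rest on the assumed SD, one correctly specified normal score, sites without true effects, and complete follow-up. Strong covariates are plausible, since the article records NIHSS, GCS and stroke subtype at baseline, but it gives no figure for their strength. The gain does not repair the shortfall in sample size.

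**What to change.** Add to the statistical plan that, from the planned logistic model for day-90 poor outcome, the standardized (marginal) risk difference and risk ratio will be reported with delta-method or bootstrap 95% confidence intervals, alongside the adjusted odds ratio and the crude risk difference. State that the main NNT is for poor outcome and is derived from that risk difference. If an NNT for death is still wanted, it needs its own analysis of death and should be labelled as such.

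Cost: two or three sentences and a short script, because this may lie outside the standard menus of the named SPSS version. No new data are needed. The downside is that weakly prognostic covariates would bring little or no gain, or a slight loss; keeping the crude estimate in the report makes that visible.

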### Protocol amendments

Protocol amendments will be agreed upon with the CHASE Study Group, Sponsor and Funding Body before submission for ethical approval. Following ethical approval, protocol modifications will be communicated with relevant parties such as the trial investigators, the trial registry, and, if required, trial participants.

### Dissemination policy

The results of this trial will be disseminated to a wide clinical audience (patients, health professionals, policy makers, and the general public) through publication in a high-impact international scientific journal.

## Discussion

A few multicenter, randomized studies have been carried out to search for the ideal BP range for patients with acute stroke; however, none of them aimed at severe stroke, which has a much higher rate of mortality and disability. No clinical evidence can be used to guide the BP management in critical care for those stroke patients with an initial presentation of severe neurological deficits. Our study aims to test the superiority of individualized BP lowering compared to guideline-recommended BP lowering in improving three-month outcome. Our study will provide the first evidence on the optimum BP-lowering target for patients with acute severe stroke.

Factors that contribute to raised BP in acute stroke are multifaceted, such as history of hypertension, stroke severity, pressure response to hospital admission, infarct area related to BP adjustment, and increased intracranial pressure [19]. Raised BP later falls into the following types: without antihypertensive medications BP declines spontaneously; with antihypertensive medications BP does not decline, declines modestly (10–15% from baseline), or intensively (≥ 20% from baseline value) [20]. Elevated BP raises the risk of cerebral edema, hemorrhagic transformation of the infarct [21], hematoma expansion [22], cardiac complications, and renal insufficiency. On the other hand, a decrease in BP might reduce the blood perfusion of the brain and aggravate the cerebral ischemic injury, especially in large territorial ischemia [23]. One clinical study indicated that both large increase and reduction in BP (> 20 mmHg) were associated with a higher risk of early neurological deterioration, increased infarct volume, and poorer outcome at three months [24]. Therefore, a proper management of BP is essential for stroke patients.

However, no ideal BP range has been scientifically determined yet. Guidelines for AIS from the American Heart Association (AHA)/American Stroke Association suggest that BP targets are based on best clinical judgment and a reasonable estimate might be to lower the SBP by 15% if the BP is > 220/120 mmHg [15]. For ICH patients presenting with SBP < 180 mmHg, guidelines from AHA in 1999 suggest to defer antihypertensive therapy; guidelines from AHA in 2015 suggest to lower SBP to 140 mmHg. Chinese guidelines for AIS recommend the use of hypertensive therapy when SBP is > 200 mmHg [14]. Also, Chinese guidelines for ICH suggest that antihypertensive therapy should be initiated when SBP is > 180 mmHg and a target around 160/90 mmHg can be considered although evidence is lacking [25]. None of the above guidelines mentioned any BP-lowering regimen specifically for severe stroke due to the lack of clinical evidence.

Given the paucity of studies on BP management for severe stroke, we performed a retrospective preliminary study in stroke patients admitted to neurological intensive care unit (NICU) in Xijing Hospital (a tertiary teaching hospital) in the last three years and found that NICU mortality was significantly higher in patients with SBP reduced by > 15% than those with SBP reduced by < 15%. This difference of mortality remained significant in patients with AIS. For ICH, the NICU mortality was also higher in patients with SBP reduced by > 15% than those with SBP reduced by < 15%, albeit insignificant.

Based on the above result and previous studies, we designed a multicenter RCT to investigate whether individualized lowering (10–15% reduction from admission level) of elevated BP would improve the outcomes in patients with severe stroke, hoping to provide evidence of BP management for acute severe stroke, help improve the quality of life, and reduce family and social burdens.

